## Abstract

**Background:**

Tuberculosis (TB) is transmitted in bioaerosols containing *Mycobacterium tuberculosis* (*Mtb*). Despite being central to ongoing TB transmission, no routine diagnostic assay exists to measure *Mtb* in bioaerosols. Furthermore, published studies of *Mtb* in bioaerosol samples have been limited to individuals with sputum-positive pulmonary TB. Notably, TB diagnosis is based on clinical symptoms and sputum laboratory findings. This is despite the fact that approximately half of all patients commencing TB treatment are sputum-negative, resulting in a high proportion of presumptive treatments. Here, we propose to use a sensitive air sampling protocol to investigate the prevalence of *Mtb*-containing bioaerosols in both sputum-positive and sputum-negative TB suspects, at the same time evaluating the potential to identify unrecognized transmitters of TB.

**Methods:**

Our parallel-group design will identify viable *Mtb* in bioaerosols produced by individuals attending a TB clinic in South Africa. Sampling will be performed on eligible individuals presenting with symptoms indicative of TB and repeated at 14 days if initially positive. Participants will be prospectively classified into three distinct groups based on National TB Control Program (NTBCP) criteria: Group A, TB notification with sputum-based laboratory confirmation; Group B, TB notification with empiric diagnosis; and Group C, individuals not notified. Group C individuals with detectable *Mtb* bioaerosol will be monitored until resolution of clinical and laboratory status. Collection of bioaerosol specimens will be via two consecutive sampling modalities: (1) direct sampling following a specific respiratory manoeuvre; and (2) indirect sampling during passive respiratory activity. Bioaerosol specimens will be analyzed for viable *Mtb* using DMN-trehalose staining and live-cell fluorescence microscopy. *Mtb* genomes and mycobacterial and host lipids will be detected using droplet digital PCR and mass spectrometry analyses, respectively. The primary objective is to determine the prevalence of *Mtb* bioaerosols in all TB clinic attendees and in each of the groups. Secondary objectives are to investigate differences in prevalence of *Mtb* bioaerosol by HIV status and current isoniazid preventive therapy (IPT) use; we will also determine the impact of anti-TB chemotherapy on *Mtb*-containing bioaerosol production.

**Discussion:**

Respiratory bioaerosol has a potential role in non-invasive TB diagnosis, infectivity measurement and treatment monitoring.

**Trial registration:**

ClinicalTrials.gov: NCT04241809. Date of Registration: 27/1/2020.

## Background

Tuberculosis (TB), which is caused by the obligate human pathogen, *Mycobacterium tuberculosis* (*Mtb*), is the foremost infectious cause of death in adults globally [1]. Persistence of the TB epidemic is driven by successive cycles of infection, pulmonary disease, *Mtb* bioaerosol expulsion and inhalation by susceptible individuals. Interventions to interrupt this cycle are critical to curb the TB epidemic, however knowledge of the physical process of *Mtb* transmission is limited. This is primarily due to the paucity of investigations detecting, quantifying and characterizing *Mtb* bioaerosols. As others have highlighted [2], it remains unclear when source cases become infectious, how long after effective treatment they remain infectious, what are the respiratory mechanisms of aerosolization, and how long *Mtb* bioaerosols remain viable in the environment. Furthermore, while sputum *Mtb* positivity and presence of lung cavitation predict infectiousness, prediction is partial (and based on retrospective, epidemiological analyses) thus limiting accurate risk stratification for contact screening. To address these knowledge gaps, tools to facilitate direct detection of viable aerosolized *Mtb* bacilli in exhaled breath are urgently required.

To improve the utility of *Mtb* bioaerosol sampling, it is essential to maximize detection yield. Three key elements to consider are: (1) patient bioaerosol production; (2) an efficient bioaerosol collection apparatus; and (3) the *Mtb* detection modality. Previous bioaerosol studies have used a spectrum of sampling approaches. These include subjects coughing into an apparatus for 10 min with culture-based detection [3], sitting passively in a chamber for 1 h with a combination of culture and PCR detection [4], and wearing a modified face mask for 10 min to 5 h with PCR detection [5, 6]. Though instructive, these studies have been limited to individuals with sputum-positive pulmonary TB, with detection yields ranging from 28 to 77%. This range of outcomes can be attributed to the spectrum of inter-individual infectiousness; however, the unknown variance in intrinsic sensitivity of each of the systems is likely to be more significant. Put simply, the absence of *Mtb* bioaerosol in a sampled individual may only indicate *Mtb* numbers below the detection threshold of the sampling system, rather than non-production. Consequently, optimizing all elements of the sampling process is essential to identify *Mtb* bioaerosol in paucibacillary individuals. Critical factors include the site in the respiratory tract of bioaerosol generation [7], bioaerosol volume obtained, and the limit of detection of the technique used to identify the organism. Bioaerosol specimen volumes are likely to be in the order of nanolitres so, even with *Mtb* bacilli concentrations greater than in sputum [4], standard assays may be inadequate.

This study will assess an optimized bioaerosol sampling system based on the previously described Respiratory Aerosol Sampling Chamber (RASC) [8]. Patient-derived bioaerosol generated by specific respiratory manoeuvres will be directly captured to maximize aerosol volume. In addition, passive respiratory activity within a chamber with indirect air sampling will be used to capture bioaerosol with transmission potential. A high-flow, wet-walled cyclone collector will be used for both methods, ensuring the capture of a large proportion of the exhaled air volumes with extraction of the bioaerosol into liquid. The liquid specimen will then be subjected to live-cell fluorescence imaging to identify single viable *Mtb* bacilli based on DMN-trehalose probe incorporation patterns and differential bacterial cellular morphology [9].

### Aim

The aim of this study is to identify viable *Mtb* bacilli in exhaled bioaerosol from individuals attending a TB clinic in Cape Town, South Africa. The specific objectives are divided into primary, secondary and exploratory.

#### Primary objective

To compare the prevalence proportions of *Mtb*-containing bioaerosol in sputum-positive and sputum-negative pulmonary TB cases (Groups A & B).

#### Secondary objectives

2.To quantify the numbers of viable *Mtb* organisms in bioaerosols per litre of air sampled and per nanolitre of bioaerosol particulate volume collected in both sputum-positive and sputum-negative pulmonary TB cases (Groups A & B).

#### Exploratory objectives

3.To determine the prevalence of *Mtb*-containing bioaerosols in TB suspects not diagnosed with clinical TB (Group C).4.To determine the prevalence and numbers of viable *Mtb* in subjects receiving or not receiving IPT prophylaxis.5.To determine the prevalence and numbers of viable *Mtb* in subjects with and without HIV co-infection.6.To determine the prevalence and numbers of viable *Mtb* in subjects before and after TB therapy.7.To determine the numbers of viable *Mtb* in bioaerosols collected by direct and indirect sampling.8.To determine the ratio of *Mtb* genomes (ddPCR) to viable *Mtb* organisms (DMN-tre positivity) in *Mtb*-containing bioaerosols.9.To identify which *Mtb* and host lipids are present in *Mtb*-containing bioaerosols.

## Methods

### Study design

This study will utilize a pragmatic, parallel group design (Fig. 1). All participants who meet the eligibility criteria will be invited to have bioaerosol sampling performed at the Aerobiology Research Centre (ARC) prior to TB investigations or treatment. An induced sputum sample will be collected, cultured and stored for future downstream studies before bioaerosol sampling. Classification into three groups will be based on the outcome of routine clinical practice at the TB clinic implementing the National TB Control Program (NTBCP) [10]. Group A will comprise patients with TB notification and sputum-based laboratory confirmation (GeneXpert positive sputum or sputum culture if performed); Group B will consist of patients with TB notification without sputum-based laboratory confirmation (physician diagnosed cases with GeneXpert negative sputum and negative sputum culture if performed); and Group C will contain individuals who are not notified. Repeat bioaerosol sampling will be conducted after 14 days on participants in all groups with initial bioaerosol samples containing viable *Mtb*. Group C individuals will be re-evaluated clinically, with induced sputa and repeated bioaerosol sampling at monthly intervals until two consecutive samples are negative or treatment is commenced.

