### Study population

Consecutive patients with respiratory and/or constitutional symptoms suggestive of pulmonary TB who self-present to either of two local TB clinics will be offered recruitment into the study. The expected timeline to recruit the target number of patients is 1–2 years.

The eligibility criteria are:
age over 13 years (corresponding to increasing TB prevalence)suspected TBwritten, informed consent (parental consent and patient assent for those aged under 18 years)

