### Statistical analysis

Historical clinic data suggest individuals suspected of TB divide into groups A, B, and C in the ratio 3:5:10. Based on this ratio, a sample size of 250 TB clinic attendees will give a 90% power to detect a 20% bioaerosol yield in Group B. Assuming 100% bioaerosol yield in Group A, this gives an absolute difference of 12.5% between sputum and bioaerosol yields in notified TB cases (two-sided *p* < 0.05).

Demographic (age, sex, BMI, HIV status) and microbiology data will be entered into a secure RedCap Database. To maintain confidentiality, participant identifying information will be removed. All analyses will be based on the groups to which patients are originally assigned. Analyses of the primary and secondary aims will be by comparison of paired proportions using McNemar’s test or comparison of independent proportions using a chi-square test. Mixed effect models can be used to adjust comparisons for any potential confounding variables.

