To our knowledge, bioaerosol sampling in sputum-negative pulmonary TB cases has not been performed previously, despite evidence of transmission from this group [15–18]. We are therefore extending attempts to detect bioaerosol to patients with notified TB without sputum microbiological confirmation (Group B). Expectorated sputum, the primary specimen for pulmonary TB diagnosis, has significant limitations [19]. Globally, only 56% of pulmonary TB cases are bacteriologically confirmed by sputum testing [20]. The remainder, who are diagnosed by clinical symptoms or chest radiography, do not accumulate *Mtb* bacilli in sputum, or do not produce sputum, or do not expectorate adequately. Poor quality sputum samples are a particular problem in children and in HIV-infected individuals, leading to suboptimal diagnostic sensitivity. The finding of culture or Xpert MTB/RIF positivity in bronchoalveolar lavage from sputum-negative or sputum-scarce patients [21–23] suggests that *Mtb* is frequently present in the peripheral airways. The bronchiole fluid film burst method of bioaerosol generation [7] rapidly and non-invasively samples this biofluid with comparable biosafety to induced sputum. We aim to provide preliminary data on the clinically relevant role of bioaerosol sampling as a novel diagnostic specimen.

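### Group B sets no site of disease, so extrapulmonary-only notifications can be counted as sputum-negative pulmonary TB and may dilute the Group B yield

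*Protocol article*

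**What the plan says.** The Primary objective concerns "sputum-positive and sputum-negative pulmonary TB cases (Groups A & B"; the Secondary objectives section uses the same equation of groups with pulmonary disease.

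The Study design section gives the rule that assigns people: "Group B will consist of patients with TB notification without sputum-based laboratory confirmation", with the parenthetical limit "physician diagnosed cases with GeneXpert negative sputum and negative sputum culture if performed". The Abstract words it as "Group B, TB notification with empiric diagnosis", and the Discussion as "patients with notified TB without sputum microbiological confirmation (Group B". None of the three names a site of disease.

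Recruitment, under Study population, takes "Consecutive patients with respiratory and/or constitutional symptoms suggestive of pulmonary TB". The eligibility list beneath it asks only for suspected TB, an age limit and consent. The Statistical analysis section keeps participants in the group to which they were first assigned.

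**The concern.** The objective names one population and the assignment rule selects another that may be wider. Take a participant who presents with constitutional symptoms thought to suggest pulmonary TB, has a negative sputum GeneXpert, and is then diagnosed by a physician and notified with extrapulmonary TB only. This person meets the Group B rule as written, and no stated step removes them or analyses them apart.

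The misclassification can go only one way. Group A requires positive sputum, so an extrapulmonary-only case cannot enter it. If these cases shed less, Group B alone is lowered and the A-B difference grows. A low Group B yield would then have two explanations that the data could not separate: either bioaerosol sampling misses sputum-negative pulmonary disease, or part of the group had no pulmonary disease. The Discussion presents sampling of sputum-negative pulmonary TB as new, so this is the estimate that most needs a clear meaning.

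**Working it through.** **Inputs from the Statistical analysis section.** 250 attendees; "individuals suspected of TB divide into groups A, B, and C in the ratio 3:5:10"; a 20% yield in Group B; a 100% yield in Group A; a stated difference of 12.5 points between sputum and bioaerosol yields in notified cases.

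**Assumed inputs, not in the article.** A share *f* of Group B is extrapulmonary-only, shown for 10%, 20% and 30%. The yield is 20% in pulmonary cases and 0% in extrapulmonary-only cases. Zero gives the largest dilution; any yield between 0% and 20% gives less.

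**Step 1: the plan's own figure.**
- A = 250 × 3/18 = 41.7; B = 250 × 5/18 = 69.4; A + B = 111.1.
- Bioaerosol positives in B = 0.20 × 69.4 = 13.9.
- Gain = 13.9 / 111.1 = 12.5 points. This reproduces.

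**Step 2: rule as written.** Group B yield = (1 − *f*) × 20%. Gain = 69.4 × (1 − *f*) × 0.20 / 111.1.

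**Step 3: extrapulmonary-only cases excluded.** The positives are the same, but the denominator shrinks: gain = 69.4 × (1 − *f*) × 0.20 / [41.7 + 69.4 × (1 − *f*)].

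| *f* | Group B yield, as written | Positives in B | Gain, as written | Notified cases after exclusion | Gain after exclusion |
|---|---|---|---|---|---|
| 10% | 18% | 12.5 | 12.5/111.1 = 11.3 | 41.7 + 62.5 = 104.2 | 12.0 |
| 20% | 16% | 11.1 | 11.1/111.1 = 10.0 | 41.7 + 55.6 = 97.2 | 11.4 |
| 30% | 14% | 9.7 | 9.7/111.1 = 8.8 | 41.7 + 48.6 = 90.3 | 10.8 |

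After exclusion the Group B yield is 20% in every row. With Group A at 100%, the A-B difference is 80 points after exclusion, against 82, 84 and 86 points as written.

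**Step 4: power.** Exact McNemar power for sputum against bioaerosol in notified cases, with discordance in one direction only:

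| *f* | As written (n = 111) | After exclusion |
|---|---|---|
| 10% | 98.9% | 98.9% (n = 104) |
| 20% | 97.1% | 97.2% (n = 97) |
| 30% | 93.0% | 93.2% (n = 90) |

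The two agree closely because the expected number of discordant pairs is the same. With *f* = 0 the exact power is 99.6%, so the stated 90% does not reproduce under this test. That is a separate matter and does not bear on this point.

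**The case against.** The strongest reply is that the article, read as a whole, describes a cohort of pulmonary suspects. Recruitment is limited to symptoms suggestive of pulmonary TB, the objectives call both groups pulmonary, and the Discussion introduces Group B as the extension to sputum-negative pulmonary cases. On this view one word is missing from one sentence. The article also condenses a fuller protocol and bases grouping on routine programme outcomes, so the handling of site may be set out elsewhere.

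Part of this stands. The recruitment filter and the limit to physician-diagnosed, sputum-negative cases must reduce the number of extrapulmonary-only cases that reach Group B, and that number may be small. It would be wrong to say that Group B takes every unconfirmed notification. The filter does not close the gap, though: it applies before investigation, constitutional symptoms can satisfy it, and the final diagnosis may differ from the presenting suspicion. Nor is this a detail left to another document. The article states the group rule, and that rule does not match the objective it serves.

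A reader might also see a conflict between the Abstract's empiric diagnosis and the Study design wording for disease proven on a non-sputum specimen. That reading is weak: Study design says physician diagnosed, which naturally describes the same people.

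**Conclusion.** The point holds as a mismatch between the objective and the assignment rule. Extrapulmonary-only cases can enter Group B, cannot enter Group A, and would lower the Group B prevalence if their yield is lower. Under the assumptions above, the Group B yield falls by 2, 4 or 6 points. The notified-case gain is about 0.7, 1.4 or 2.0 points below its value in the population that the objective names. The share and the zero yield are assumptions; the article supplies neither.

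Four stronger readings are not supported:
- That such cases do enter and do depress the yield. The article shows only that they can enter.
- That a large HIV-infected share makes this likely. Comparisons by HIV status are planned, but no share is given.
- That the planned 20% and 12.5 points are too low for pulmonary cases. The 20% is a yield to be detected, with no sign that it came from a mixed population.
- That the loss should be measured from 12.5 points. Excluding these cases also shrinks the denominator, so 12.0, 11.4 and 10.8 are the right comparators.

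The consequence is for the meaning of the Group B prevalence and the A-B comparison, not for power.

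**What to change.** In Study design, define Group B as participants notified with pulmonary TB, with or without extrapulmonary disease, whose routine sputum is negative. Take site of disease from the notification record. Report participants notified with extrapulmonary TB only in a separate descriptive summary, outside both the A-versus-B comparison and the notified-case yield. Bring the Abstract and Discussion definitions into line; the objectives can then stand as written.

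The cost is a wording change, one field copied from the notification record, and a somewhat smaller Group B: 62.5, 55.6 or 48.6 instead of 69.4 at the illustrated shares. Sampling and the routine clinic pathway are untouched.

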## Discussion

The implications of bioaerosol positivity in people with suspected pulmonary TB differ depending on the subgroup sampled. Prevalence in patients with sputum-confirmed TB (Group A) establishes the sensitivity of bioaerosol sampling comparable with previous studies [3–5]. This will validate the optimized bioaerosol sampling system and allow a comparison between the direct and indirect aerosol generation methods. The direct method – performing a respiratory manoeuvre into a cone apparatus – captures nascent bioaerosol from the lung periphery and upper airway structures. The short time-interval between mouth and collector (approx. 40 msec) reduces losses of large particles by gravitational settling and maximizes the bioaerosol volume captured. Therefore, this approach aims to capture all *Mtb* organisms produced from the respiratory tract regardless of potential role in transmission. In contrast, the indirect capture method samples an aged bioaerosol product from the close breathing zone of the patient. The smaller size distribution of bioaerosol following drop-out of the larger diameters and desiccation to hygroscopic equilibrium has the capacity to penetrate the lungs of susceptible contacts. It follows, therefore, that this bioaerosol has the greatest propensity for disease transmission. Furthermore, enumeration of viable *Mtb* bacilli derived from this method may more closely reflect host infectivity, as similar investigations have related high numbers of *Mtb* colony forming units in cough aerosols to increased infection rates in household contacts [14]. Using the indirect method, we intend to explore the effect of treatment on organism numbers longitudinally by repeat sampling of patients with bioaerosol positivity in groups A and B. Also, by identifying the subset of HIV-infected individuals already receiving IPT at enrolment we will be able to assess the effect of isoniazid monotherapy on *Mtb* bioaerosol production.

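### Only initially positive participants are re-sampled at day 14, so the before/after-therapy comparison leans toward a fall and cannot by itself show a chemotherapy effect

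*Protocol article*

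**What the plan says.** All references are to the protocol article.

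- **Who is repeated.** Study design: "Repeat bioaerosol sampling will be conducted after 14 days on participants in all groups with initial bioaerosol samples containing viable" *Mtb*. The Abstract agrees: sampling is "repeated at 14 days if initially positive". The rule covers Groups A, B and C.
- **What is claimed.** The Abstract, listing secondary objectives, says "we will also determine the impact of anti-TB chemotherapy on" bioaerosol production. The body places the matching aim, objective 6, under Exploratory objectives; it covers both prevalence and numbers of viable organisms "in subjects before and after TB therapy".
- **How it would be examined.** The Discussion, referring to Groups A and B, says: "Using the indirect method, we intend to explore the effect of treatment on organism numbers longitudinally by repeat sampling of patients with bioaerosol positivity".
- **What a negative means.** Background accepts that a negative sample may reflect "numbers below the detection threshold of the sampling system, rather than non-production".
- **Which test.** Statistical analysis names McNemar's test or a chi-square test for the primary and secondary aims. It names no test for exploratory aims.

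The article does not mention selection on the first result or regression to the mean, and it does not name Group C as a comparator for the treatment question.

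**The concern.** A participant enters the paired data only if the first sample was positive. That sets baseline overall positivity at 100% by construction and leaves nobody who could move from negative to positive. On the article's own account of its detection limit, some producers will be missed on any one occasion, so some initial positives will repeat negative without any treatment effect. The same selection favours first counts that happened to be high, so the mean second count is expected to be lower.

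At stake is the sentence in the Abstract about the impact of chemotherapy. A before/after fall in this set mixes any treatment effect with a selection effect of unknown size, and nothing in the stated analysis separates the two.

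**Working it through.** **The plan's own figure.** No figure is given for the before/after comparison. The planning values for the primary objective supply the numbers of positives. With 250 attendees split 3:5:10:

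- A = 250 × 3/18 = 41.7; B = 250 × 5/18 = 69.4; C = 250 × 10/18 = 138.9.
- Stated yields are 100% in A and 20% in B. Then 0.20 × 69.4 = 13.9, and 13.9/111.1 = 12.5%, which reproduces the stated difference.
- Initial positives in A and B: 41.7 + 13.9 = 55.6, about 56.

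**Prevalence, no treatment effect.** Let q be the probability that an initial positive repeats negative for reasons unrelated to treatment. The article does not give q, so the values below are assumptions. With one discordant cell empty, the exact two-sided McNemar p-value for d changes is 2 × 0.5^d: 0.0625 at d = 5 and 0.031 at d = 6. Significance therefore needs six or more repeat negatives, with probability P(Bin(n, q) ≥ 6).

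| Initial positives in A+B | q = 5% | q = 10% | q = 20% | q = 30% |
|---|---|---|---|---|
| 56 (A yield 100%) | 6% | 49% | 98% | >99.9% |
| 46 (A yield 77%) | 3% | 31% | 92% | 99.8% |
| 26 (A yield 28%) | 0.2% | 4% | 42% | 84% |

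The lower rows use the 28 to 77% range of earlier yields quoted in Background for Group A, with B kept at 20%: 0.77 × 41.7 + 13.9 = 46.0 and 0.28 × 41.7 + 13.9 = 25.6.

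A 100% yield in A does not sit well with q above zero. Setting the Group A yield to 1 − q gives 51, 47 and 43 positives at q = 10%, 20% and 30%, and probabilities of 40%, 93% and 99.6%.

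**Counts, no treatment effect.** Two exchangeable Poisson counts were simulated per person with lognormal means, keeping only people whose first count exceeded zero. Assumed between-person log SD was 0.5 to 1.5 and within-person log SD 0 to 1.

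| Median bacilli per sample | Fall in mean count | Positive on repeat |
|---|---|---|
| 1 | 7–32% | 64–78% |
| 3 | 2–12% | 84–93% |
| 10 | 0–2% | 93–100% |

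For example, at a median of 1 with SDs of 0.5 and 0, the mean goes from 1.80 to 1.27, and 1 − 1.27/1.80 = 29%. Across all settings, 21 to 47% of individuals showed a rise in count. The last column corresponds to q of 22–36%, 7–16% and 0–7%, so the assumed q values lie within what this model produces at low bacillary numbers.

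**What selection hides.** In the same simulation, 34 to 96% of first-sample negatives would be positive on a second sample. These upward changes offset the downward ones when everybody is re-sampled, making the expected change zero.

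**The case against.** Several stronger readings are tempting, and the article does not support them.

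- **That the comparison can only show a fall.** This holds for overall prevalence. It does not hold for counts, which are half of objective 6 and the focus of the Discussion. Individual counts can rise; the mean is biased, not bounded. Nor does it hold for indirect-sample positivity: entry is by any positive initial sample, so someone positive only by direct sampling could become indirect-positive at day 14.
- **That a significant decline is nearly certain.** That needs q of roughly 20% or more together with the larger yields. At q = 5% with 56 positives the chance is 6%, close to nominal.
- **That McNemar is the planned test.** It is assigned to primary and secondary aims. It reaches this comparison only through the Abstract's label, since the body calls the objective exploratory. The probabilities above are therefore conditional on its use.
- **That collection conditions differ between visits.** Study design says "An induced sputum sample will be collected, cultured and stored for future downstream studies before bioaerosol sampling" and mentions induced sputa again at Group C re-evaluation. It is silent on repeats in Groups A and B. A condensed article may leave this to the full protocol, so no difference can be inferred and no change of order is called for.
- **That the fall will be read as a drug effect.** This is a prediction. The Discussion says only that the effect will be explored.

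It is also fair to say that following positives is a reasonable way to study persistence of shedding, that untreated Group C positives are already repeated at 14 days, and that the primary objective is untouched. These points lower the severity. They do not remove the bias, and no later analysis can supply day-14 data on participants who were not re-sampled.

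**Conclusion.** The concern stands at moderate severity. Followed as written, the plan yields a before/after comparison selected on its outcome: overall prevalence can only stay at 100% or fall, and mean counts are biased downward. The Abstract's claim about the impact of chemotherapy is not supported by that comparison alone.

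The size cannot be fixed from the article. With no treatment effect it ranges from negligible (a 0–2% fall in mean count near 10 bacilli per sample; a 6% chance of significance at q = 5% with 56 positives) to decisive (a 7–32% fall near 1 bacillus; 98% at q = 20%). These figures rest on the planning yields, assumed values of q, assumed variances and, for the probabilities, use of an exact McNemar test on overall positivity.

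**What to change.** 1. **Name the comparator.** Prespecify the 14-day change in bioaerosol-positive Group C participants who are still untreated. They enter under the same selection rule and are already due for sampling. Report the treated-minus-untreated difference in change, for positivity and for counts. State that it will be imprecise, because Group C may yield few positives, and that the groups differ clinically, so it is not a randomised contrast. Cost: analysis text only.
2. **Restate the aim.** Reword objective 6 and the Abstract as persistence of bioaerosol positivity and counts at day 14 among initially positive participants, with no causal claim from the within-treated fall. Give the objective the same rank, secondary or exploratory, in both places. Cost: wording only.

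Re-sampling a random subset of initially negative Group A and B participants would let upward changes be seen. It needs extra sampling sessions, so it is a resource decision and not a condition of the fix.
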